
|  |   |                                        |    |                                      |                 |    |    |
|--|---|----------------------------------------|----|--------------------------------------|-----------------|----|----|
|  |   |                                        | 4  | W14/16                               | 18 mg           |    |    |
|  |   |                                        | 12 | W18/20/22/24/26/28                   | 24 mg           |    |    |
|  | 4 | GZR18-48 mg                            | 2  | W0                                   | 3 mg            | 65 | 13 |
|  |   |                                        | 4  | W2/4                                 | 6 mg            |    |    |
|  |   |                                        | 4  | W6/8                                 | 12 mg           |    |    |
|  |   |                                        | 4  | W10/12                               | 24mg            |    |    |
|  |   |                                        | 4  | W14/16                               | 36 mg           |    |    |
|  |   |                                        | 12 | W18/20/22/24/26/28                   | 48 mg           |    |    |
|  | 5 | once - weekly
GZR18-24 mg (18 mg) * | 2  | W0/1                                 | 3 mg            | 52 | 13 |
|  |   |                                        | 4  | W2/3/4/5                             | 6 mg            |    |    |
|  |   |                                        | 4  | W6/7/8/9                             | 9 mg            |    |    |
|  |   |                                        | 4  | W10/11/12/13                         | 12 mg           |    |    |
|  |   |                                        | 4  | W14/15/16/17                         | 15 mg           |    |    |
|  |   |                                        | 12 | W18/19/20/21/22/23/24/25/26/27/28/29 | 24 mg (18 mg) * |    |    |

\*Note: If the subjects in the 18 mg once a week group of the original 3.0 version protocol do not agree to enter the 24 mg once a week group, the 18 mg dose will still be administered from W18 to W29.

- Early termination visit (ET)  
Randomized subjects who withdraw from the clinical study due to meeting the withdrawal criteria need to complete ET visit as much as possible.

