|                           | 
hours, 120 hours, 168 hours after administration (overlapping with the sparse blood sampling time point at W30, no need to repeat collection), 240 hours, 336 hours (W31), and 504 hours (W32). There are a total of 12 blood sampling time points, but two of them overlap with sparse blood sampling time points.
 
Time points of immunogenic blood sampling:
 
 
• Within 1 hour before the first administration (W0D0); within 1 hour before administration at W16; in the W30 visit morning of the study end/early termination; in the morning of the last safety follow-up for W33. Each group has 4 blood sampling time points.
 
 
Time points of Glycated hemoglobin (HbA1c) blood sampling:
 
During the screening period, blood samples are collected in the morning of the W30 study visit. Each group has 2 blood sampling time points.
 
Time points of fasting blood glucose and insulin blood sampling:
 
During the screening period, blood samples are collected in the morning of the W30 study visit. Each group has 2 blood sampling time points.
 
Time points of safety indicators blood sampling:
 
The safety blood sampling indicators here include blood routine, blood biochemistry, blood amylase, blood lipase, coagulation function, calcitonin, thyroid stimulating hormone, free triiodothyronine, and free thyroxine. The time point for blood pregnancy test detection is detailed in the flowchart.
 
Screening period; within 1 hour before administration of W8, W12, W16, W20, and W24; W30/ET Visit Morning; blood samples are collected in the morning of the last safety follow-up for W33. Each group has 8 blood sampling time points.
 |

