| Fasting blood glucose, insulin                         | X         |          |             |     |                |     |                |     |                |      |                |                |      |                |      |                | X    |                  |                   |
| Glycosylated hemoglobin                                             | X         |          |             |     |                |     |                |     |                |      |                |                |      |                |      |                | X    |                  |                   |
| IWQoL-Lite-CT questionnaire                                         |           | X        |             |     |                |     |                | X   |                |      |                |                |      | X              |      |                | X    |                  | X                 |
| SF-36 questionnaire                                                 |           | X        |             |     |                |     |                | X   |                |      |                |                |      | X              |      |                | X    |                  | X                 |
| PK blood sampling                                      |           | X        |             |     | X a |     | X b |     | X c |      | X d | X e |      | X f | X    | X g | X    |                  |                   |
| Randomization                                                       |           | X        |             |     |                |     |                |     |                |      |                |                |      |                |      |                |      |                  |                   |
| Hospital Administration                                |           | X        | X           | X   | X              | X   | X              | X   | X              | X    | X              | X              | X    | X              | X    | X              |      |                  |                   |

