12. Immunogenicity: Including anti-drug antibody (ADA) and neutralizing antibody (NAb), sampling point: within 1 h before the first administration (W0D0); W16 within 1 h before administration; the morning of W30 study completion/early termination (ET) visit; W33 last safety follow-up morning.
13. Body measurements: For the same subject, weight and waist circumference should be measured under as consistent circumstances as possible (in a fasting state with clothes of similar thickness) each time. Body height is measured only during the screening period to calculate BMI.
14. Fasting blood glucose, fasting insulin, glycosylated hemoglobin: screening period, blood samples are collected in the morning after the W30 study.
15. Time points of pharmacokinetic blood sampling:
  - Time points of sparse blood sampling:
  - ✓ Dose group 1 (s.c. 12 mg once every two weeks): Within 1 hour before the first administration (W0D0); within 1 hour before the first administration (W6) of the previous dose of the target dose; within 1 hour before reaching the target dose for administration (W10); within 1 hour before the 6th administration of the target dose (W20) and 72 hours  $\pm$  1 hour after administration; within 1 hour before administration at W26 and W28; blood samples are collected in the morning of the end of study visit (W30). There are a total of 8 blood sampling time points.
  - ✓ Dose group 2 (s.c. 18 mg once every two weeks): Within 1 hour before the first administration (W0D0); within 1 hour before the first administration (W10) of the previous dose of the target dose; within 1 hour before reaching the target dose for administration (W14); within 1 hour before the 6th administration of the target dose (W24) and 72 hours  $\pm$  1 hour after administration; within 1 hour before administration at W26 and W28; blood samples are collected in the

morning of the end of study visit (W30). There are a total of 8 blood sampling time points.

- ✓ Dose group 3 (s.c. 24 mg once every two weeks): Within 1 hour before the first administration (W0D0); within 1 hour before the first administration (W14) of the previous dose of the target dose; within 1 hour before reaching the target dose for administration (W18); within 1 hour before the 6th administration of the target dose (W28) and 72 hours  $\pm$  1 hour after administration; blood samples are collected in the morning of the end of study visit (W30). There are a total of 7 blood sampling time points

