##### **Secondary endpoints:**

##### **Efficacy endpoints**

- Proportion of subjects who achieved (yes/no) body weight reduction  $\geq 5\%$ , 10%, 15%, 20% from baseline.
- The changes from baseline in body weight, waist circumference, waist to hip ratio (waist/hip circumference), and BMI.
- The percentage change from baseline in body weight (%) after drug withdrawal at the last safe follow-up (W33).
- The changes from baseline in glucose metabolism indicators: HbA1c, FPG, fasting insulin, HOMA-IR and HOMA- $\beta$ .
- The changes from baseline in cardiovascular disease risk factors: blood pressure (systolic and diastolic blood pressure), pulse, TC, LDL-C, HDL-C, and TG.
- The changes from baseline in the impact of weight on quality of life score reported by patients: the total and individual scores of the IWQOL-Lite-CT, the total and individual scores of the physical and psychological parts of SF-36 scoring table.

---

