### **9.7 Handling of dropouts or missing data**

Subjects who provide at least one efficacy variable data during the treatment period are included in the primary analysis. If a subject early terminates the study prior to the end of the treatment period, his/her last efficacy variable data will be collected for analysis.

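### HbA1c, fasting glucose and fasting insulin are not drawn at early termination, so subjects who leave before week 30 have no post-baseline glycaemic value

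*Protocol*

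**What the plan says.** Section 3.2 lists the affected secondary endpoints: "The changes from baseline in glucose metabolism indicators: HbA1c, FPG, fasting insulin, HOMA-IR" and HOMA-beta. That is three assays and two indices derived from them.

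The sampling schedule is given in three places in the protocol, and they agree:

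- Section 1.1, biological sample collection, once for HbA1c and once for fasting glucose and insulin: "During the screening period, blood samples are collected in the morning of the W30 study visit. Each group has 2 blood sampling time points". The two time points are screening and week 30.
- Section 1.2 flowchart: the row "Glycosylated hemoglobin" and the row for fasting glucose and insulin are each marked at V1 (screening) and V17 (week 30) only. The week-33 and ET cells are empty.
- Section 1.2, note 14: "Fasting blood glucose, fasting insulin, glycosylated hemoglobin: screening period, blood samples are collected in the morning after the W30 study".

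Other blood samples in the same part of section 1.1 do cover early leavers. Safety bloods are taken at "W30/ET Visit Morning", and immunogenicity samples "in the W30 visit morning of the study end/early termination". Withdrawn subjects "need to complete ET visit as much as possible".

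Section 9.4 analyses continuous secondary endpoints by the primary method, an ANCOVA with baseline as covariate. Section 9.7 includes in the primary analysis subjects with at least one efficacy value from the treatment period. For a subject who terminates early, it says that "his/her last efficacy variable data will be collected for analysis".

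**The concern.** Effects on glucose metabolism are a stated secondary objective, yet this is the one secondary efficacy block measured at week 30 that is not also measured at ET. Someone who withdraws before week 30 contributes a screening value and nothing afterwards. A statistical analysis plan can choose how to handle the gap, but it cannot recover a measurement that was never scheduled.

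The missing values are unlikely to be a random subset. Under the dose adjustment standards and section 5.3, subjects who do not tolerate an adverse event at doses up to 12 mg are withdrawn. Those who do not tolerate a higher dose may step down and stay. Withdrawal is thus linked to tolerability. It can differ between GZR18 and placebo, and between titration schedules, since the 48 mg group reaches 12 mg at week 6 and the other groups at week 10. A comparison restricted to subjects who reach week 30 does not keep the full protection of randomization.

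**Working it through.** **Step 1: the plan's own count.** Counting marks from V1 to V18 and ET in the two flowchart rows gives V1 and V17, so two draws. This reproduces the two time points stated in section 1.1 and matches note 14. Three agreeing statements make a table-extraction error implausible.

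**Step 2: can another scheduled test supply the value?** No. The biochemistry panel in flowchart note 7, which is drawn at ET, lists neither glucose nor insulin, and HbA1c is not in any other panel. The OGTT is done at screening only.

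**Step 3: comparison with the other secondary efficacy measurements (flowchart).**

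| Measurement | Week 30 | ET |
|---|---|---|
| Body measurements (weight, waist) | yes | yes |
| Vital signs (blood pressure, pulse) | yes | yes |
| Lipids (within biochemistry) | yes | yes |
| IWQOL-Lite-CT, SF-36 | yes | yes |
| HbA1c | yes | no |
| Fasting glucose, insulin | yes | no |

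**Step 4: how many subjects.** Inputs from section 9.8: 20% dropout, 52 active and 13 placebo subjects in four groups, 65 active and 13 placebo subjects in the 48 mg group.

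- Total: 4 × (52 + 13) + (65 + 13) = 260 + 78 = 338, as stated.
- Active: 4 × 52 + 65 = 273. Placebo: 5 × 13 = 65.
- Expected without a post-baseline glycaemic value = dropout × N.

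| Dropout | Active (273) | Placebo (65) | Total (338) |
|---|---|---|---|
| 10% (assumed) | 27.3 | 6.5 | 33.8 |
| 20% (planned) | 54.6 | 13.0 | 67.6 |
| 30% (assumed) | 81.9 | 19.5 | 101.4 |

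Per group at 20%, this is 10.4 of 52 active subjects (13 of 65 in the 48 mg group) and 2.6 of 13 placebo subjects.

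**Step 5: what section 9.7 does with them.** Its first sentence asks for a value from the treatment period. Applied to each variable, a subject with only a screening HbA1c does not qualify, and the analysis covers only those with a week-30 value. Its second sentence, taken alone, would carry the last value forward, and for these tests that is the screening value. The two sentences do not lead to the same result for this block, and the first fits the wording better.

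**The case against.** Several points against the concern stand.

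- These are secondary, supportive measures. Previously diagnosed diabetes and diabetic-range glucose at screening are exclusions, and the primary endpoint is untouched because weight is measured at ET.
- The 20% is a planning allowance, with no breakdown by group or timing. The 68 is also a ceiling on what an ET draw could recover, because subjects lost to follow-up would still have no value.
- An ET value is not a week-30 value. Carrying one forward after a few weeks of titration is itself a substitute for the 30-week effect.

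A reader might also infer stronger things that the documents do not support.

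- *Dropouts are imputed as no change, shrinking the effect to 80%.* The arithmetic (1 − 0.20 = 0.80) needs the second sentence of 9.7 read without the first, and equal 20% dropout in both arms. Section 9.7 also speaks of the primary analysis. Section 9.4 carries the analysis method over to secondary endpoints but does not expressly carry over 9.7.
- *The planned repeated-measures model fails.* Section 9.4 plans it for the main efficacy indicators only, so nothing planned for the glycaemic endpoints fails.
- *Only about 10 placebo subjects per group remain because of the schedule.* Section 9.8 already assumes 10 evaluable placebo subjects per group. If placebo is pooled across groups, about 65 − 13 = 52 remain.
- *A mid-study draw such as week 16 would cover most dropouts.* No dropout timing is given. The withdrawal rule applies at doses up to 12 mg, all groups reach 12 mg by week 10, and section 4.2.1 reports adverse events concentrated early in escalation. Many tolerability withdrawals could come before week 16.

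What remains is the sampling gap itself, which none of these points removes.

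**Conclusion.** The point holds as an inexpensive improvement to the sampling schedule. Subjects who leave before week 30 have no scheduled post-baseline HbA1c, fasting glucose or fasting insulin, so HOMA-IR and HOMA-beta cannot be calculated for them either. On the more natural reading of section 9.7, the five glycaemic analyses are restricted to those who reach week 30, a group selected partly by tolerability.

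The size is up to about 68 of 338 subjects at the planned 20% dropout, and about 34 to 101 at an assumed 10% to 30%. These figures assume that the planned rate applies to the whole trial and that dropouts leave before the week-30 draw. The direction and size of any bias cannot be derived from the protocol, because it gives no dropout by group and no expected glycaemic change.

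**What to change.** Add HbA1c, fasting glucose and fasting insulin to the ET column of the section 1.2 flowchart, to the two sampling lists in section 1.1, and to note 14. If the entry is worded as week 30 or ET, as it already is for the safety bloods, the stated count of two time points per group can stay. No new visit is needed: biochemistry is already drawn at ET, and section 7.1 specifies it as fasting.

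The cost is three routine assays for each withdrawn subject who attends. The benefit is partial, because ET attendance is requested only as far as feasible. ET values should be recorded as such, not relabelled as week-30 values.

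Adding the assays to one existing mid-study draw is optional. It would give some later dropouts an on-treatment value, but it should not be presented as covering most of them.

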#### Analysis sets

**Full Analysis Set (FAS):** FAS includes all randomized subjects who received at least one dose of the investigational drug. The data set is the main analysis set of demographic data, baseline indicators, medical history and curative effect.

**Per Protocol Set (PPS):** PPS is a subset of FAS, which includes subjects who met all inclusion criteria, did not meet exclusion criteria, had primary endpoint efficacy indicators and did not have other major protocol deviations. The data set is used for the supportive analysis of efficacy.

**Safety Set (SS):** SS includes all randomized subjects who received at least one dose of investigational drug and had at least one safety evaluation. This data set is used for statistical analysis of safety indicators.

**PK Concentration Set (PKCS):** PKCS includes all randomized subjects who received at least one dose of investigational drug and had at least one measured plasma concentration of the investigational drug available after medication.

**PK Parameter Set (PKPS):** PKPS includes all randomized subjects who received at least one dose of the investigational drug and had at least one valid PK parameter of the investigational drug during the study.

#### Descriptives

The continuity data will be described by non-missing observations, mean, median, standard deviation, minimum and maximum. The classification data will be described by frequency and percentage. For the calculation of percentage, the denominator will be the population of relevant subjects (unless otherwise specified).

Baseline is defined as the last non-missing measurement before the first use of investigational drug (unless otherwise specified).

#### Efficacy evaluation

hypothesis-testing:

|                 |                                                                                   |
|-----------------|-----------------------------------------------------------------------------------|
|                 | Percentage change in body weight from baseline to W30 (one-sided $\alpha=0.025$ ) |
| Null hypothesis | $H_0: \mu_T - \mu_C \geq 0$                                                       |

|                        |                                                                                                                                                                                                                                                                                                                                                                                                                                                                                                                                                                                                                                                                                                                                                                                                                                                                                                                                                                                                                                                                                                                                                                                                                                                                                                                                                                                                                                                                                                                                                                                                                                                                                                                                                                                                                                                                                                                                                                                                                                                                                                                                                                                                                                                                                                                                                                                                                                                                                                                                                                                                                                                                                                                                                                                                                                                                                                                                                                                                                                                                                                                                                                    |                        |                          |
|------------------------|--------------------------------------------------------------------------------------------------------------------------------------------------------------------------------------------------------------------------------------------------------------------------------------------------------------------------------------------------------------------------------------------------------------------------------------------------------------------------------------------------------------------------------------------------------------------------------------------------------------------------------------------------------------------------------------------------------------------------------------------------------------------------------------------------------------------------------------------------------------------------------------------------------------------------------------------------------------------------------------------------------------------------------------------------------------------------------------------------------------------------------------------------------------------------------------------------------------------------------------------------------------------------------------------------------------------------------------------------------------------------------------------------------------------------------------------------------------------------------------------------------------------------------------------------------------------------------------------------------------------------------------------------------------------------------------------------------------------------------------------------------------------------------------------------------------------------------------------------------------------------------------------------------------------------------------------------------------------------------------------------------------------------------------------------------------------------------------------------------------------------------------------------------------------------------------------------------------------------------------------------------------------------------------------------------------------------------------------------------------------------------------------------------------------------------------------------------------------------------------------------------------------------------------------------------------------------------------------------------------------------------------------------------------------------------------------------------------------------------------------------------------------------------------------------------------------------------------------------------------------------------------------------------------------------------------------------------------------------------------------------------------------------------------------------------------------------------------------------------------------------------------------------------------------|------------------------|--------------------------|
|                        | 
 
 Alternative hypothesis	<math>H_1: \mu_T - \mu_C < 0</math>	
 
 
<math>\mu_T</math> is the mean percentage change of body weight from baseline in the first to fifth dose groups after 30 weeks of GZR18 treatment (<math>\mu_T</math> includes <math>\mu_{T1}</math>, <math>\mu_{T2}</math>, <math>\mu_{T3}</math>, <math>\mu_{T4}</math> and <math>\mu_{T5}</math>, which corresponds to GZR18 s.c. 12 mg once every two weeks, GZR18 s.c. 18 mg once every two weeks, GZR18 s.c. 24 mg once every two weeks, GZR18 s.c. 48 mg once every two weeks and GZR18 s.c. 24 mg once-weekly respectively), <math>\mu_C</math> is the mean percentage change of body weight from baseline in the first to fifth dose groups after 30 weeks of placebo treatment. <math>\alpha</math> is significance level (Type I error rate).
 
Primary endpoint analysis: the percentage of body weight change (%) from baseline at week 30 will be taken as the primary endpoint, which will be analyzed based on the covariance model (ANCOVA), where, with baseline body weight as the covariate and group as the fixed effect, and the change from baseline is the dependent variable. The following indicators will be then calculated: the least-squares mean (LSMean) and its two-sided 95% CI of the percentage of the change from baseline in both groups, as well as the LSMean difference between the treatment and control groups and its two-sided 95% CI.
 
Secondary endpoint analysis: The continuity variables will be analyzed by the same method as the primary endpoint analysis. The number of cases reaching the target end point and the rate of reaching the target and its two-sided 95% CI will be counted in the analysis of the proportion between the two groups. At the same time, the rate difference between the two groups (the investigational drug group and the placebo group) and its two-sided 95% CI will be calculated. The rate of reaching the target and the two-sided 95% CI of the rate difference between the two groups will be calculated by the Clopper-Pearson Exact method.
 
Sensitivity analysis
 
Sensitivity analysis of main efficacy indicators.
 
 
1. The Mixed Model Repeated Measures (MMRM) method will be used to incorporate all time points from baseline to week 30 into the Linear Mixed model (LMM) as a supporting analysis to compare the efficacy differences between the treatment group and the placebo group.
 
2. Consistent with the primary endpoint analysis method, some specific populations will be excluded for comparison of efficacy between groups.
 
 
Statistical analysis of safety endpoints
 
Adverse events will be summarized for each treatment group using Medical Dictionary for Regulatory Activities (MedDRA) according to System Organ Class (SOC) and Preferred term (PT). All adverse events are presented in the form of a list,
 | Alternative hypothesis | $H_1: \mu_T - \mu_C < 0$ |
| Alternative hypothesis | $H_1: \mu_T - \mu_C < 0$                                                                                                                                                                                                                                                                                                                                                                                                                                                                                                                                                                                                                                                                                                                                                                                                                                                                                                                                                                                                                                                                                                                                                                                                                                                                                                                                                                                                                                                                                                                                                                                                                                                                                                                                                                                                                                                                                                                                                                                                                                                                                                                                                                                                                                                                                                                                                                                                                                                                                                                                                                                                                                                                                                                                                                                                                                                                                                                                                                                                                                                                                                                                           |                        |                          |

|  |                                                                                                                                                                                                                                                                                                                                                                                                                                                                                                                                                                                                                                                                                                                                                                                                                                                                                                                                                                                                                                                                                                                                                                                                                                                                                                                                                                                                                                                                                                                                                                                                                                                                                                                                                                                                                                                                                                                                                                                                                                                                                                                                                                                                                                                                                                                                                                                                                                                                                                                                                                                                                                                                                            |
|--|--------------------------------------------------------------------------------------------------------------------------------------------------------------------------------------------------------------------------------------------------------------------------------------------------------------------------------------------------------------------------------------------------------------------------------------------------------------------------------------------------------------------------------------------------------------------------------------------------------------------------------------------------------------------------------------------------------------------------------------------------------------------------------------------------------------------------------------------------------------------------------------------------------------------------------------------------------------------------------------------------------------------------------------------------------------------------------------------------------------------------------------------------------------------------------------------------------------------------------------------------------------------------------------------------------------------------------------------------------------------------------------------------------------------------------------------------------------------------------------------------------------------------------------------------------------------------------------------------------------------------------------------------------------------------------------------------------------------------------------------------------------------------------------------------------------------------------------------------------------------------------------------------------------------------------------------------------------------------------------------------------------------------------------------------------------------------------------------------------------------------------------------------------------------------------------------------------------------------------------------------------------------------------------------------------------------------------------------------------------------------------------------------------------------------------------------------------------------------------------------------------------------------------------------------------------------------------------------------------------------------------------------------------------------------------------------|
